### Treatments

Before randomization, all patients will have received two retreatment cycles of Lutathera® (7.4 GBq infusion each, separated by 8 weeks) (Fig. 1). A radiological tumor assessment will be performed after two cycles. Patients with progression during the first sequence of Lutathera® retreatment will be considered as screen failure and will be followed until the end of the study.

### Randomization and masking

Randomization (1:1) will be performed using EnnovClinical software. Patients will be randomized to the experimental arm, consisting of two additional cycles of Lutathera® (7.4 GBq infusion each, separated by 8 weeks), or the control arm with no treatment (active surveillance) (Fig. 1).

### Statistical considerations

A median PFS of 15 months [11] after two cycles of Lutathera® for retreatment corresponds to around a 65% disease control rate 6 and 10 months from randomization and inclusion, respectively. To detect a minimal difference of 20% in disease control rate at 6 months post-randomization (65% vs. 85%) between the control and experimental groups, respectively, with a power of 80% and a 5% two-sided significance level, a total of 146 patients is required for randomization (73 patients per arm). Non-evaluable patients will be considered as failure. We estimate that around 176 patients will need to be included to ensure that 146 patients are randomized.

All analyses will be performed on an intention-to-treat (ITT) basis, defined as all randomized patients, while the safety population will comprise all treated patients who received at least one dose of treatment after inclusion. The primary endpoint will also be analyzed in the per-protocol (PP) population, defined as all eligible patients (patients with no major violations of the inclusion/non-inclusion criteria) and evaluable patients (randomized treated patients with a minimum of two evaluations).

Categorical variables will be reported with numbers and frequencies and continuous variables with medians and ranges. Qualitative variables will be compared using chi-square or Fisher’s exact tests, while quantitative variables will be compared using the Kruskal-Wallis test. The DCR will be reported using percentages and 95% confidence intervals (CI) (binomial exact method). Event-free survival (PFS, OS) will be estimated using the Kaplan-Meier method and compared using the stratified log-rank test. Statistical analyses will be performed using STATA 16.0 (StatCorp, College Station, TX, USA) and SAS 9.4 software.

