Principal exclusion criteria will include: no response (i.e., no complete response [CR], partial response [PR], or stable disease [SD]) to “first PRRT”; radiological progression after two cycles of “Second PRRT” according to RECIST version 1.1; G4 hematotoxicity and/or nephrotoxicity during the initial PRRT, or unresolved adverse events categorized as G2 or higher (as per the CTCAE v5.0 from previous PRRT cycles or any other therapy for NET, excluding alopecia and peripheral neuropathy); pancreatic NET; neuroendocrine carcinoma; patients with prior external beam radiation therapy to > 25% of the bone marrow; severe renal impairment (GFR according to the Modification of Diet in Renal Disease < 40 mL/min or nephrotic syndrome) or hepatic insufficiency (alanine aminotransferase/aspartate aminotransferase > 2.5 x the upper limit of normal [ULN], or > 5 x ULN if liver function abnormalities are due to the underlying malignancy, and/or total serum bilirubin > 2.5 x ULN); any other uncontrolled concomitant disease or brain metastases (unless they have been treated and stabilized for at least 24 weeks prior to enrolment in the study; patients with a history of brain metastases must have had a head CT scan with contrast or MRI to document stable disease prior to enrolment in the study); history of another solid tumor in the 5 years before inclusion, apart from treated and controlled cancer in the cervix and skin cancer (basal or squamous cell).

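### The 65% control rate behind the 146-patient sample size describes all included patients; among those actually randomized the same 15-month median implies about 76%, so 80% power for an 85% experimental rate does not follow

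*Protocol article*

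**What the plan says.** The protocol article, Statistical considerations, starts from "A median PFS of 15 months [11] after two cycles of Lutathera® for retreatment" and states that this "corresponds to around a 65% disease control rate 6 and 10 months from randomization and inclusion, respectively". One rate is thus attached to two time points, which differ by 4 months: the interval from inclusion to randomization.

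The same section sets the target at 65% versus 85% disease control 6 months after randomization, described as a minimal difference of 20 percentage points, "with a power of 80% and a 5% two-sided significance level". This leads to 146 randomized patients, 73 per arm. It adds: "We estimate that around 176 patients will need to be included to ensure that 146 patients are randomized". Non-evaluable patients count as failures, and the analysis set is all randomized patients.

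Two other sections fix who can be randomized. Under Treatments: "Patients with progression during the first sequence of Lutathera® retreatment will be considered as screen failure". Under Patients, the exclusion criteria include "radiological progression after two cycles of “Second PRRT” according to RECIST version 1.1". Study design and objectives counts the primary endpoint from randomization.

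**The concern.** Ten months from inclusion and 6 months from randomization are the same moment for a given patient, but the two rates have different denominators. The 10-month rate from inclusion is taken over everyone included, and so counts as failures those who progress in the first 4 months. The trial's own rules remove those patients before randomization, so they cannot appear in the control arm. The rate among the patients who remain must be higher.

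The control rate is one of the two inputs that set the size of the primary comparison. If it is really about 76%, an experimental arm that reaches the planned 85% is only about 9 points better. The trial would then probably give a non-significant result although the treatment had met its stated target, and that result could be misread as showing no benefit from two further cycles.

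**Working it through.** **Inputs.** From Statistical considerations: median PFS 15 months; 65% versus 85%; two-sided 5%; 80% power; 73 per arm; 176 included for 146 randomized. The 4-month gap is 10 − 6. The exponential form is my assumption.

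**1. The plan's sample size.** The pooled-variance formula without continuity correction, with mean rate 0.75, gives

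n = [1.96·√(2·0.75·0.25) + 0.842·√(0.65·0.35 + 0.85·0.15)]² / 0.20² = 72.4, so 73 per arm and 146 in total.

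The chi-square test with 73 per arm, its power obtained by enumerating both binomials, has 81% power. The stated figure reproduces from the stated rates.

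**2. Where 65% comes from.** With S(t) = 0.5^(t/15):

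- S(4) = 0.831
- S(6) = 0.758
- S(10) = 0.630

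Only S(10), in all included patients, is near 65%. For an exponential rate of 65% at 6 months from randomization, the median would have to be 6·ln 2 / (−ln 0.65) = 9.7 months, not 15.

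**3. The rate among randomized patients.** Conditional on being progression-free at month 4: S(10)/S(4) = 0.630/0.831 = 0.758.

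- *Shape.* Weibull curves with a 15-month median and shapes from 0.7 to 2 give 75% to 78%.
- *Time origin.* If the 15 months run from the end of the two cycles, the rate is S(6) = 75.8% again.
- *Share of the loss that is progression.* The planned loss is 1 − 146/176 = 17.0%. If half of it is progression, 91.5% are progression-free at randomization. The rate is then 0.630/0.915 = 69%, or 0.65/0.915 = 71% if S(10) is taken as 65%. If all of it is progression and S(10) is 65%, the rate is 0.65/0.830 = 78%.

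**4. Power with 73 per arm** (same test as in step 1). The hazard ratio is ln(experimental rate)/ln(control rate).

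| Control | Experimental | Basis for the experimental rate | Hazard ratio | Power |
|---|---|---|---|---|
| 65% | 85% | as stated | 0.38 | 81% |
| 75.8% | 85% | stated rate kept | 0.59 | 29% |
| 75.8% | 90.1% | hazard ratio kept | 0.38 | 65% |
| 75.8% | 92.5% | rate that reaches about 80% | 0.28 | 82% |
| 75.8% | 95.8% | 20-point difference kept | 0.16 | 96% |
| 69% | 85% | half the loss is progression | 0.44 | 64% |
| 71% | 85% | same, S(10) = 65% | 0.48 | 53% |
| 78% | 85% | all the loss is progression, S(10) = 65% | 0.67 | 18% |

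The normal approximation gives nearly the same values: 80%, 29% and 63% in the first three rows, 94% in the fifth, and 80% power at an experimental rate of 92.6%.

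**The case against.** **Power need not be lost.** The section states its target both as 85% and as a minimal 20-point difference. If the difference is what matters, 73 per arm has more than enough power at a 76% control rate. This stands as far as it goes: the documents do not say which quantity is to be held. A reader might infer that the trial is simply underpowered, at 29%. That is too strong, because 29% holds only at the stated 85%. Keeping 20 points, however, requires about 96% disease control and a hazard ratio near 0.16, against 0.38 in the plan's own scenario, and the article offers no support for an effect of that size.

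**Non-evaluable patients count as failures, which lowers the observed control rate.** True, and the 76% is before any such reduction. But bringing 75.8% down to 65% needs 1 − 0.65/0.758 = 14% non-evaluable. The article gives no such percentage and attributes the 65% to the median PFS alone. The rule would also lower the experimental rate: with 5% to 10% non-evaluable in both arms (an assumption) and the hazard ratio kept at 0.38, power is about 52% to 43%.

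**The source of the 15 months cannot be checked here.** Its population and time origin are unknown, so 76% is a model value. It is nonetheless what the stated median implies, under either time origin and over a wide range of curve shapes.

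**Early progressors may have been counted twice.** Because 146/176 = 0.830 almost equals S(4) = 0.831, a reader might infer that the plan removed them through the inflation to 176 and again through the 65%. The documents do not establish this. An ordinary 20% inflation, 146 × 1.2 = 175.2, leads to 176 equally well, and the Discussion names toxicity as well as progression as a cause of early withdrawal. The point above does not need it.

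**Conclusion.** The concern holds for the control rate and, conditionally, for the power. The 65% is an all-included rate applied to a group from which the early progressors have been removed. The stated median implies about 76% in the randomized control arm, with about 69% to 78% as the range over the share of pre-randomization loss that is progression and over S(10) of 63% or 65%. The low end is cautious, since it lowers early progression while holding the 10-month rate fixed.

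The claim that 73 per arm gives 80% power for an 85% experimental rate therefore does not follow from the plan's own inputs. At 76% control, power is about 29% for 85% and about 65% at the plan's implied hazard ratio. It reaches 80% only at an experimental rate of about 92.5%. It passes 80% comfortably only under the 20-point reading. The conclusion rests on the exponential form and on the 4-month gap that the article itself implies.

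**What to change.** In Statistical considerations:

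1. State the control rate for patients progression-free at randomization: about 76%, range about 69% to 78%, before any reduction for non-evaluable patients. Say what share of the loss from 176 to 146 is expected to be progression.
2. Justify the experimental rate against that control rate, and say whether the target is an absolute rate, a difference or a relative effect.
3. Replace the single 80% power statement with what 146 patients deliver: about 29% for 76% versus 85%, about 65% at a hazard ratio of 0.38, and 80% at about 76% versus 92.5%. Note that the 20-point reading needs about 96% and a hazard ratio near 0.16.

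The cost is a change of wording and a less favourable stated power. No additional patients are needed for the restatement.

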## Methods

### Study design and objectives

ReLUTH will be a prospective, multicenter, randomized, controlled, open-label, phase II trial performed throughout France (Fig. 1 and Additional file 1). The primary objective will be to evaluate the efficacy of two additional cycles of Lutathera® (one injection every two months) compared to active surveillance during 6 months in patients who have already been retreated with two cycles. The primary endpoint will be the disease control rate (DCR) at 6 months from randomization (defined as Complete Response, Partial Response, and Stable Disease in the Response Evaluation Criteria In Solid Tumours (RECIST) v1.1) with an evaluation every 2 months.

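### The per-protocol set's two-evaluation minimum can drop known early failures, and its 'treated' condition does not measure adherence to the assigned arm

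*Protocol article*

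**What the plan says.** All references are to the protocol article.

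- **Endpoint and schedule** (Study design and objectives): the primary endpoint is the disease control rate 6 months after randomization, "with an evaluation every 2 months".
- **Main analysis** (Statistical considerations): the analysis set is all randomized patients, and those who cannot be evaluated count as failures.
- **Per-protocol analysis** (same section): the primary endpoint is analysed a second time in patients without major eligibility violations who are also "evaluable patients (randomized treated patients with a minimum of two evaluations". The text does not say whether the assessment before randomization counts as one of the two evaluations. It makes no exception for progression or death.
- **Treatment before and after randomization**: under Treatments, both arms receive two retreatment cycles before randomization. Under Randomization and masking, the comparator is then "the control arm with no treatment (active surveillance".
- **Use of 'treated'** (Statistical considerations): the safety set applies the word to anyone given one or more doses since inclusion. The same section places inclusion about 4 months before randomization (10 months from one equals 6 months from the other).

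**The concern.** Disease control is an endpoint on which early progression and early death are failures. A rule that admits a patient only after a second evaluation can remove the patients who failed soonest, and does so because they failed. The same patient is then a failure in the intention-to-treat analysis and absent from the per-protocol analysis, although the outcome is known. The rule also misses in the other direction: a patient stable at months 2 and 4 with nothing at month 6 meets the minimum without a 6-month status.

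A per-protocol set should also pick out patients who were managed as assigned. If 'treated' is satisfied by the cycles given before randomization, an experimental patient who received neither additional cycle passes.

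At stake is the supporting analysis of the primary endpoint. It would overstate disease control in both arms, and more in the arm with more early failures. A per-protocol result weaker than the intention-to-treat result could then be an artefact of the set definition.

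**Working it through.** **1. The plan's own figure.** Inputs from Statistical considerations: "To detect a minimal difference of 20% in disease control rate at 6 months post-randomization (65% vs. 85"%), "with a power of 80% and a 5% two-sided significance level", and "a total of 146 patients is required for randomization (73 patients per arm"). With pooled variance and no continuity correction:

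n per arm = [1.960·√(2·0.75·0.25) + 0.842·√(0.65·0.35 + 0.85·0.15)]² / 0.20² = 72.4, rounded up to 73, or 146 in total.

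Power at 73 per arm is 80.3%. The figure reproduces, and the per-protocol rule does not enter it.

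**2. Who leaves under each reading of the minimum.**

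| Reading | Progression seen at month 2 | Death before month 2 | Death between months 2 and 4, no progression at month 2 |
|---|---|---|---|
| Both evaluations after randomization, assessments stop at progression | dropped | dropped | dropped |
| Both after randomization, assessments continue | kept if the month-4 evaluation is done | dropped | dropped |
| Pre-randomization assessment counts as one | kept | dropped | kept |

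Every reading drops some certain failures. Only the first drops month-2 progressors as a group.

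**3. Size under the first reading.** Assumptions: constant hazard to month 6 in each arm, and every failure by month 2 dropped. Later deaths without progression are ignored, because the article gives no death rate.

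- Control: still controlled at month 2 = 0.65^(1/3) = 0.866. Dropped = 13.4%, or 73 × 0.134 = 9.8 patients.
- Experimental: 0.85^(1/3) = 0.947. Dropped = 5.3%, or 73 × 0.053 = 3.8 patients.
- Per-protocol disease control: 0.65/0.866 = 75.0% and 0.85/0.947 = 89.7%.
- Difference: 14.7 points instead of 20, a loss of 5.3.
- Share of failures removed: 0.134/0.35 = 38% and 0.053/0.15 = 35%.
- Power in the reduced set: about 61%.

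**4. Size under the other readings.** Month-2 progressors stay in as failures. Only early deaths and patients without enough evaluations leave, so the shrinkage is about 0 points.

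**5. Dependence on timing.** Without constant hazards the share of failures dropped may differ by arm. Dropping one half of control and one third of experimental failures gives 0.788 vs 0.895, a difference of 10.7 points. The reverse gives 0.736 vs 0.919, or 18.3 points. These shares are arbitrary and only show that the figure in step 3 rests on its assumption.

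**6. 'Treated'.** Every randomized patient has had two cycles before randomization, and inclusion comes before those cycles. Read as in the safety set, the condition is met by all 146 patients and separates nobody in either arm.

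**The case against.** A reader might infer that requiring treatment empties the control arm. The article does not support this. Controls have received two cycles since inclusion, and the sentence just before the per-protocol definition uses 'treated' in that sense. The control arm is empty only if the word means treated after randomization, which is not stated. What remains is that the condition does no work.

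A reader might also take 75.0% vs 89.7% as the expected result. It is an upper illustration. It needs both evaluations to fall after randomization, assessments to stop at progression, and a constant hazard. The article states none of these; under Patients it has everyone followed for 60 months, although it does not say that imaging continues. The plan's other input also gives a smaller loss: with a 15-month median and constant hazard, month-2 progression in control is 1 − 0.5^(2/15) = 8.8%, about 6 of 73 rather than 10. Early deaths should be few, since a life expectancy of at least 6 months is required and patients progressing during the first two cycles are not randomized.

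The per-protocol analysis is supplementary. In the illustration it moves against the experimental arm, so it does not manufacture a benefit. Finally, operational detail of analysis sets is often left to the full protocol or analysis plan, neither of which is shown.

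Most of this stands and limits the size. It does not remove the point: the two-evaluation minimum is a printed rule, and as printed it has no exception for known failures.

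**Conclusion.** The point holds as a minor one, with moderate confidence. As worded, per-protocol membership for the primary endpoint depends on the outcome, and 'treated' does not test adherence to the assigned arm.

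The design difference of 20 points would shrink in the per-protocol set by between about 0 points (if the pre-randomization assessment counts, or assessments continue after progression) and about 5 points (if neither applies). Both figures rest on the plan's 65% and 85% and on constant hazards, which is an assumption. The intention-to-treat result, where early failures stay counted, and the 146 randomized patients do not depend on this rule.

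**What to change.** - Delete the two-evaluation minimum. Define evaluable as having a 6-month RECIST status, or earlier documented progression or death, counted as failure.
- Replace 'treated' with adherence by arm, relative to randomization. Experimental: started the assigned additional cycles. Control: managed as assigned, without study Lutathera before month 6 or progression.
- State how an experimental patient who progresses or dies before the first additional cycle is classified, so that the adherence condition does not bring the same selection back.

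The cost is analysis-set wording only, with no extra patients, visits or sample-size change. Because the trial is open-label, the wording should be fixed before outcome data by arm are examined.

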Clinical practice regarding the number of new cycles is heterogeneous and most teams perform only two additional cycles (every 8 weeks), which were recently showed to be safe and effective [5]. The few studies to evaluate retreatment have been cohort studies. There is a need for a prospective trial to assess the effectiveness, safety, and quality of life after four cycles of retreatment with Lutathera® in patients with intestinal progressive SSTRi + NET, with the objective of a higher disease control rate. Accordingly, we plan to study the impact of two additional cycles compared to a controlled arm in active surveillance in the ReLUTH (retreatment with Lutathera®) trial. Different stratification factors will be used in the study, as follows: (a) the time of disease control after the “first” PRRT (< 18 months vs. ≥ 18 months) – patients with a history of a durable PFS after initial PRRT tend to have long-lasting PFS after salvage treatment (*p* = 0.04) [9]; (b) type of progression (radiologic vs. no radiologic); (c) renal function (glomerular filtration rate (GFR) < 60 mL/min vs. ≥ 60 mL/min), as it may have an impact on disease control [9] and OS [6]; (d) intercurrent line of treatment between “first” and “second” PRRT, as it is currently unclear (Yes vs. No).

The results of our prospective, randomized, controlled study may lead to new recommendations for the use of PRRT in patients with intestinal progressive SSTRi + NET. ReLUTH would provide strong statistical data to confirm that in patients retreated for intestinal progressive NET, two additional cycles of Lutathera® will be safe and effective compared to only two cycles and will have a beneficial impact on quality of life. If our hypothesis is confirmed, the results of our study would be able to prolong life and improve quality of life in patients.

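### The only stated test that can apply to the primary disease control rate ignores the four stratification factors, and no interval for the between-arm difference is stated; adjusting would gain about 0 to 4 points of power

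*Protocol article*

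**What the plan says.** The Background of the protocol article introduces the factors with "Different stratification factors will be used in the study, as follows". They are:

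- duration of disease control after the first PRRT (below 18 months, or 18 months and more);
- type of progression (radiologic or not);
- GFR (below 60 mL/min, or 60 and more);
- treatment between the first and second PRRT (yes or no).

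A link with outcome is cited for duration of control (p = 0.04, no effect size) and, more cautiously, for renal function. The fourth factor is described as unclear, and no reason is given for the second.

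Randomization and masking states that "Randomization (1:1) will be performed using EnnovClinical software" and does not repeat the factors. I read them as factors of the randomization, which fits the stratified test used later.

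Statistical considerations then gives three rules:

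- General comparisons: "Qualitative variables will be compared using chi-square or Fisher’s exact tests".
- Primary endpoint, reporting: "The DCR will be reported using percentages and 95% confidence intervals (CI) (binomial exact method").
- PFS and OS: "compared using the stratified log-rank test".

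The sample size is 146 (73 per arm), for 65% versus 85% DCR, "with a power of 80% and a 5% two-sided significance level". Non-evaluable patients count as failures.

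**The concern.** The factors enter the analysis of the secondary time-to-event endpoints but, as far as the text goes, not that of the primary endpoint. Stratified allocation balances the arms on these factors. If they predict disease control, the true variance of the difference is smaller than the one an unadjusted test uses. The test then rejects too rarely under the null and gives up power that the design has already paid for.

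Two smaller matters belong with this. The primary objective is comparative and the design target is a 20-point difference, yet the stated interval describes one arm at a time. And the choice between chi-square and Fisher is left open for the test that decides the trial, although the two differ in power at this sample size.

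**Working it through.** **1. The plan's own figure.** Inputs from Statistical considerations: p1 = 0.65, p2 = 0.85, mean 0.75, two-sided 5% (z = 1.960), 80% power (z = 0.842). Uncorrected two-proportion formula:

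n per arm = [1.960·√(2·0.75·0.25) + 0.842·√(0.65·0.35 + 0.85·0.15)]² / 0.20²
= [1.960·0.6124 + 0.842·0.5958]² / 0.04
= (1.200 + 0.501)² / 0.04 ≈ 72.4, rounded up to 73.

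This gives 146 in total, as stated. With continuity correction the formula gives 83 per arm. The stated size therefore rests on the uncorrected, unstratified chi-square.

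**2. Exact properties at 73 per arm, ignoring strata** (enumeration of all outcome pairs):

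| Test | Power, 65% vs 85% | Size at common rate 65% / 75% / 85% |
|---|---|---|
| Uncorrected chi-square | 80.8% | 4.9% / 4.9% / 5.0% |
| Fisher | 75.4% | 3.3% / 3.2% / 2.9% |

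**3. Would Fisher be chosen?** Under the design rates the pooled failure rate is 1 − 0.75 = 0.25, so expected failures are 73 × 0.25 ≈ 18 per arm. That is far above the customary threshold of 5.

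**4. Effect of ignoring the strata.** Four binary factors give 2⁴ = 16 cells, or 146/16 ≈ 9 patients per cell. Simulation with 100,000 trials per setting. Assumptions not in the article: permuted blocks of 4 within cells, factor prevalences of 50/50/25/50%, the same odds ratio for every factor, and marginal DCR held at 65% and 85%. The comparator is Cochran-Mantel-Haenszel (CMH) over the 16 cells.

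| Odds ratio per factor | Control DCR, lowest to highest cell | Size: chi-square / CMH | Power: chi-square / CMH |
|---|---|---|---|
| 1 | 65% to 65% | 5.2% / 5.0% | 80.8% / 80.0% |
| 1.5 | 48% to 83% | 4.8% / 5.0% | 81.3% / 81.2% |
| 2 | 37% to 90% | 4.2% / 5.0% | 81.8% / 83.1% |
| 3 | 24% to 96% | 3.2% / 4.9% | 82.9% / 86.5% |

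CMH runs from slightly under 1 point worse to just under 4 points better. The chi-square never falls below 80%.

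**5. Adjusting by main effects instead of cells.** A risk difference adjusted for the four factors as main effects avoids the sparse cells. In a simulation with blocks of 4 and assumed prevalences, it costs essentially nothing when the factors are not prognostic (79.7% against 79.8% power). It gains about 1, 2 and 4 points at odds ratios 1.5, 2 and 3. In that run the chi-square's size was near 5% at 1.5 and about 4.3% and 3.6% at 2 and 3.

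A smaller simulation (3,000 trials for power, 6,000 for size, all prevalences 50%) agrees:

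| Odds ratio | Power: adjusted / chi-square | Gain | Size: adjusted |
|---|---|---|---|
| 1.5 | 83.2% / 81.9% | 1.3 | 4.9% |
| 2 | 84.3% / 82.2% | 2.1 | 5.3% |
| 2.5 | 86.4% / 83.1% | 3.3 | 5.3% |

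The simulation error of a 5% size here is √(0.05·0.95/6000) ≈ 0.3 points, so 5.3% is compatible with 5%.

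**The case against.** The strongest reply is that nothing stated is wrong. The chi-square after stratified randomization controls type I error, the sample size was computed for it, and it delivers the promised power. An unadjusted primary analysis in a phase II trial is a legitimate choice. The quoted sentence is a general rule that does not name DCR, the analysis plan is not shown and may specify an adjusted model, and a per-arm interval does not exclude one for the difference. All of this stands. It limits the point to an improvement of a stated method.

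The size of the gain also rests on assumptions. Block size, prevalences and odds ratios are not in the article. Eligibility narrows two contrasts: disease control of at least 12 months is required, so the short-duration stratum covers 12 to 18 months, and GFR below 40 mL/min is excluded, so the low stratum covers 40 to 60. Four equally strong factors is therefore a favourable case for adjustment, and the upper end of the range should be read as such.

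A reader might infer that the primary test is invalid, or that the trial falls short of 80% power. The figures do not support that: the loss exists only relative to an adjusted analysis. A reader might also infer a loss of about 5 points from Fisher. That would arise only if Fisher were actually used, and with about 18 expected failures per arm the usual convention points to chi-square. What remains is that the article states no rule for choosing.

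**Conclusion.** The point holds as a modest, conditional one. The article names stratification factors, gives prognostic reasons for two, uses a stratified test for PFS and OS, and states nothing comparable for the primary endpoint. The uncorrected chi-square remains valid and adequately powered. Against an analysis adjusted for the factors it forgoes about 0 to 4 points of power for assumed odds ratios of 1 to 3 per factor. Its actual size stays near 5% up to an odds ratio of 1.5 and falls to between 3% and 4% at 3. The direction follows from the balance created by stratified allocation; the amount cannot be fixed from the article. The lack of a stated interval for the difference, and of a rule for choosing between chi-square and Fisher, do not depend on these assumptions.

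**What to change.** Make the primary intention-to-treat analysis the between-arm difference in 6-month DCR, adjusted for the four stratification factors as main effects (for example a logistic model with a standardized risk difference). Report it with a two-sided p-value and a 95% CI for the difference, and keep the per-arm exact intervals as description. Prefer this to CMH over 16 cells of about 9 patients, and state in advance what is done if a factor level is nearly empty. Keep the uncorrected chi-square, on which the 146 is based, as the sensitivity analysis, and remove Fisher as an open option for the primary test.

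The cost is a change of wording and slightly more analysis work. The factors should already be known at randomization, non-evaluable patients already have an assigned outcome, and sample size and conduct are unaffected. If the factors turn out not to be prognostic, the power lost is essentially nil.
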